### Statistical analysis

Data will be obtained from all patients who complete the study protocols and follow-ups and will be analyzed using the per-protocol (PP) approach. Statistical analysis will be performed using SPSS version 20 (SPSS Inc., Chicago, IL, United States), with a significance level of *p* < 0.05. Demographics and clinical characteristics will be analyzed using descriptive statistics. Continuous and categorical data will be reported as mean values, standard deviations, number values, and percentages. Continuous variables following a normal distribution will be compared using the independent samples *t*-test, ANOVA, or rank-sum test, while categorical variables will be compared using the chi-square test.

In our RIC trial in mild Alzheimer’s dementia (*n* = 40), we implemented two strategies appropriate for small-sample longitudinal data. First, single random forest imputation was applied to address missing cognitive scores (e.g., MoCA/MMSE) by using predictors such as baseline Aβ42/Aβ40 ratio and RIC adherence preserve variable interaction structure. Second, Generalized Estimating Equations (GEE) will be used to model outcome trajectories under the assumption of missing at random (MAR), thereby accommodating incomplete data without imputation. Attrition is minimal (7% MoCA loss at 12 months) and APOE subgroup analyses show no evidence of differential dropout. This approach balances methodological rigor with feasibility and aligns with CONSORT recommendations for early-phase trials with limited resources.

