**Methods and expected results:**

This study is a randomized, controlled, single-center, prospective clinical trial designed to evaluate the safety, feasibility, and preliminary efficacy of RIC in patients with mild Alzheimer’s dementia. Eligible participants will be recruited and randomly assigned to either the RIC group or a control group receiving sham RIC, with 20 patients in each group. Participants will receive either RIC or sham RIC once daily over a 3-month period. Outcome measures will assess cognitive function, psychological well-being, and inflammatory and neurodegenerative biomarkers. Psychiatric adverse events will be monitored throughout the treatment using the Hamilton Anxiety Rating Scale (HAMA) and the Hamilton Depression Rating Scale (HAMD-17). Cognitive function and daily living abilities will be evaluated at baseline, 3 months, 6 months, and 12 months post-treatment using the Mini-Mental State Examination (MMSE), Montreal Cognitive Assessment (MoCA), Clinical Dementia Rating (CDR), and the Activities of Daily Living (ADL) scales. In addition, blood samples will be collected at each time point to measure plasma biomarkers of *β*-amyloid species and serum inflammatory cytokines to assess potential changes in cognitive decline, disease progression, and inflammation. The primary endpoint is safety, with the expectation that RIC will not increase psychiatric adverse events as reflected in HAMA and HAMD-17 scores. Primary efficacy endpoints include improvements in MMSE, MoCA, CDR, and ADL scores, indicating potential cognitive benefits and enhanced daily functioning. Secondary endpoints will analyze biomarkers to evaluate disease progression and inflammation levels before and after treatment.

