## Subjects and methods

### Study design

This study was registered on www.chictr.org.cn in November 2024 (ID: ChiCTR2400092245) and approved by the Ethics Committee of Beijing Luhe Hospital, Capital Medical University, China (2024-LHKY-092-03). All study participants were fully informed about the research process, risks, and benefits, and voluntarily agreed to participate by signing an informed consent form. The study protocol and informed consent form were approved by the Ethics Committee.

A total of 40 participants will be randomly assigned to either the observation group (RIC group) or the control group (sham RIC group), with 20 participants in each group. All participants with AD included in the study will continue receiving standard pharmacotherapy in accordance with established clinical practice guidelines. Each group will begin RIC or sham treatment, administered once daily for 45 min per session over a period of 3 months.

Specifically, our study has established a Data and Safety Monitoring Board (DSMB) composed of independent experts to ensure rigorous oversight of participant safety, data integrity, and scientific validity throughout the trial. The DSMB is responsible for regularly reviewing accumulated safety data, monitoring adverse events, and making recommendations regarding study continuation or modification as needed to protect participant welfare.

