## Outcomes

### Outcomes for safety

The primary safety outcomes of this study are to evaluate the safety profile of RIC. Specifically, the following adverse events will be monitored:

1)  Psychological and Emotional Impact: Clinical observations and previous research have highlighted that patients with AD often experience feelings of helplessness and depression as their cognitive function declines and their ability to perform daily activities diminishes. These emotional challenges can lead to anxiety and fears about disease progression. Additionally, the pressure sensation caused by RIC training may exacerbate these feelings. To address this, the psychological condition of patients will be assessed using the HAMA and the HAMD-17, and the incidence of related adverse events will be calculated.2)  Procedure Tolerability: Instances of participants being unable to tolerate either the RIC or sham RIC procedures, resulting in suspension from the study, will be recorded as adverse events.3)  Physical Injuries: Signs of tissue or neurovascular injury potentially caused by RIC or sham RIC procedures will be monitored. This includes assessments such as palpation of the distal radial artery for pulsation, visual inspection for local edema, erythema, or skin damage, and palpation for tenderness in the affected areas.4)  Vital Sign Monitoring: Participants’ vital signs, including body temperature, respiratory rate, blood pressure, and heart rate, will be recorded to identify any potential systemic effects of the intervention.

All adverse events will be reviewed and independently determined by trained members of the research team who are blinded to the randomization group. These outcomes aim to comprehensively evaluate the safety of RIC and ensure that any risks associated with the intervention are carefully monitored and managed.

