In this study, participant safety is closely monitored through structured safety management protocols. If a participant experiences psychiatric worsening, indicated by significant increases in anxiety or depression scores (HAMA or HAMD-17), an immediate referral to a psychiatrist will be initiated, and psychiatric interventions or modifications to study procedures may be recommended as appropriate. In cases of physical injury, such as tissue damage, neurovascular compromise, or significant pain related to the cuff procedure, the intervention will be immediately paused. A multidisciplinary specialist team, including experts in neurology, cardiology, neurosurgery, and vascular surgery, will promptly evaluate the participant. Treatment will be provided as needed, and the participants will be closely monitored until full resolution. Detailed records of these events will be documented and reviewed by our Data and Safety Monitoring Board (DSMB) to ensure thorough oversight and appropriate follow-up actions.

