### Sample size estimation

This is a Phase I trial measuring the safety and feasibility of RIC. Since no prior clinical studies have examined RIC in AD patients, there is no reference data available. Ganesh proposed that a cohort of 12 patients per group is sufficient to assess the safety of remote ischemic conditioning in patients with Vascular Cognitive Impairment (28). Tong’s Phase I clinical trial on the safety and efficacy of RIC in stroke patients suggested that 20 cases are sufficient to assess the feasibility of a pilot study (29). Based on studies addressing the safety and feasibility of RIC, this project targets 20 patients in each group, providing sufficient confidence to proceed to a subsequent Phase II study with a randomized sham control.

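### The completer-only analysis rule makes no exception for the primary safety endpoint, so participants who stop for intolerance fall outside the analysed safety result

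*Protocol article*

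**What the plan says.** The Statistical analysis section of the protocol article opens with its only statement of who is analysed: "Data will be obtained from all patients who complete the study protocols and follow-ups and will be analyzed using the per-protocol (PP) approach". No safety, treated or intention-to-treat set is named anywhere in the article.

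Other sections make safety the main purpose:

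- Abstract, Methods and expected results: "The primary endpoint is safety, with the expectation that RIC will not increase psychiatric adverse events as reflected in HAMA and HAMD-17 scores".
- Sample size estimation: "This is a Phase I trial measuring the safety and feasibility of RIC". The section adds that "this project targets 20 patients in each group, providing sufficient confidence to proceed to a subsequent Phase II study".
- Outcomes for safety, item 2 (tolerability): participants "unable to tolerate either the RIC or sham RIC procedures, resulting in suspension from the study, will be recorded as adverse events".
- Outcomes for safety, management text: after physical injury, "such as tissue damage, neurovascular compromise, or significant pain related to the cuff procedure, the intervention will be immediately paused".

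The second paragraph of Statistical analysis then describes single random forest imputation of missing cognitive scores, and GEE under a missing-at-random assumption that uses incomplete data without imputing them.

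**The concern.** A tolerability outcome defined by leaving the study cannot be estimated in a set defined by staying in it. The event removes the participant from both numerator and denominator. A pause after injury is a second possible route out of the completer set. Psychiatric worsening may be a third: the safety section itself expects that the cuff sensation could aggravate anxiety and low mood, and a participant who stops for that reason would take his or her HAMA and HAMD-17 data out of the comparison.

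At stake is the result that is meant to justify moving to Phase II. A tolerability failure rate that the analysis set forces to zero cannot inform that decision, and a difference between 200 mmHg and 60 mmHg cuffs in how many people stop would not show.

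For cognition, the two paragraphs of the section give different answers to the question of who is analysed. If the completer rule governs, the comparison is no longer of the groups as randomised.

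**Working it through.** **Inputs.** From the article: 20 participants per arm, 40 in total (2 × 20 = 40); analysis set = completers, per protocol; intolerance leading to suspension = primary safety event. The sample size rests on precedent, with no event rate, effect size, power or dropout rate, so there is no calculation to reproduce. The article gives no intolerance rate. The number of stops *k*, the true rate *p* and the events among stoppers below are assumptions, used only to show scale.

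**Step 1: the rate under each analysis set.** If *k* of 20 RIC participants stop for intolerance, all other participants complete, and every RIC participant started at least one session:

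- all treated: *k*/20
- completers: 0/(20 − *k*) = 0 for every *k* below 20

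Exact (Clopper-Pearson) 95% intervals:

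| Assumed *k* | All treated | Completers only |
|---|---|---|
| 1 | 1/20 = 5% (0.1% to 24.9%) | 0/19 = 0% (0% to 17.6%) |
| 2 | 2/20 = 10% (1.2% to 31.7%) | 0/18 = 0% (0% to 18.5%) |
| 3 | 3/20 = 15% (3.2% to 37.9%) | 0/17 = 0% (0% to 19.5%) |
| 5 | 5/20 = 25% (8.7% to 49.1%) | 0/15 = 0% (0% to 21.8%) |

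For *k* = 5 the completer interval ends at 21.8%, below the 25% observed among all treated.

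**Step 2: is a stop likely at this size?** P(at least one stop among 20) = 1 − (1 − *p*)^20.

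- *p* = 5%: 1 − 0.95^20 = 64%
- *p* = 10%: 1 − 0.90^20 = 88%
- *p* = 20%: 1 − 0.80^20 = 99%

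Even a low intolerance rate would probably bring the rule into play.

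**Step 3: the comparison between arms.** With 5/20 RIC stops against 0/20 sham, the two-sided Fisher test gives 2 × C(20,5)/C(40,5) = 2 × 15,504/658,008 = 0.047. Among completers the comparison is 0/15 against 0/20, 0% in both arms, and the difference has gone.

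**Step 4: other adverse events.** Suppose the three stoppers in the *k* = 3 case each also had another adverse event and one completer had one. All treated: (3 + 1)/20 = 20%. Completers: 1/17 = 5.9%.

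**Step 5: cognitive outcomes.** Here the check is a comparison of text. The first paragraph limits the data to participants who finish. The second fills in missing MoCA and MMSE scores, uses adherence as a predictor, and fits a model chosen because it tolerates incomplete follow-up. In a set of people who finished all follow-up there is little left to impute or to accommodate. The two paragraphs imply different populations, and neither is given priority.

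**The case against.** The strongest reply is that the events are not lost. The safety section says that intolerance stops are recorded as adverse events and reviewed by blinded team members, and that records of psychiatric worsening and physical injury go to the DSMB. One may argue that this specific text overrides the general completer sentence, since otherwise the tolerability outcome could never have a case. It stands that the events are captured; it would be wrong to say that the trial fails to record or monitor them. But recording and DSMB review do not decide what enters the reported comparison. The only text that does so is the completer sentence, and it has no exception for safety. Nor is this a detail left to an unseen analysis plan, because the article itself fixes the population.

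Three stronger readings are tempting, and the document does not support them:

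- **That every analysis is restricted to completers.** The GEE and imputation text points the other way for cognitive outcomes. Efficacy is therefore an internal contradiction, and loss of the randomised comparison follows under only one of the two rules.
- **That retention is 100% by construction.** The article defines no retention outcome, and it mentions attrition (7% MoCA loss at 12 months) and differential dropout, so loss is counted somewhere outside a completer set.
- **That completing means attending every daily session, so that few would qualify.** The article does not define completion, and a per-protocol threshold is commonly left to a fuller document.

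A numerical bias for the cognitive comparison would also need a dropout mechanism that the article does not supply, so none is claimed.

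**Conclusion.** The point holds for safety and tolerability. As written, the analysed rate of stopping for intolerance is 0% whatever the true rate, and other adverse events in participants who stop leave the analysed result with them. That conclusion needs only two readings: that the completer sentence applies to safety because nothing exempts it, and that a suspended participant has not completed. The scale is illustrative: an assumed 3/20 = 15% (3.2% to 37.9%) becomes 0/17.

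For cognitive outcomes the conclusion is narrower: the section contains two incompatible rules and must say which governs. The safety part needs correction before the analysis, because it concerns the primary endpoint and the case for Phase II.

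**What to change.** In Statistical analysis, replace the opening sentence with text to this effect:

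1. All safety and tolerability outcomes are analysed in all randomised participants who started at least one RIC or sham session, by arm, with the number treated as denominator.
2. Efficacy is analysed in all randomised participants, in the arm to which they were randomised, using the GEE already planned.
3. A per-protocol analysis is a sensitivity analysis, with completion defined in advance.

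This also removes the conflict with the second paragraph of the section.

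In Outcomes for safety, reconcile the wording on suspension from the study with the scheduled 3, 6 and 12 month assessments, so that outcome data are still collected where possible from participants who stop sessions. This concerns data collection only; when the procedure is stopped or paused remains a clinical matter.

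The cost is a wording change plus follow-up of a few participants at visits already scheduled. The estimated effect on cognition may be slightly diluted, because participants who received fewer sessions are included; the per-protocol sensitivity analysis remains available alongside it.

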### Neuropsychological assessments

The Mini-Mental State Examination (MMSE), Montreal Cognitive Assessment (MOCA), and Clinical Dementia Rating (CDR) scales will be used to evaluate the cognitive function of patients with mild Alzheimer’s dementia. The Activities of Daily Living (ADL) scale will be used to assess their quality of life. The Hamilton Anxiety Rating Scale (HAMA) and the Hamilton Depression Rating Scale (HAMD-17) will be used to evaluate the mental and emotional status. These assessments will be conducted at baseline, 3 months, 6 months, and 12 months.

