### Blood sample collection and analysis

Under fasting conditions, 5 mL of peripheral venous blood will be drawn, and the plasma samples will be stored in a − 80°C freezer. Enzyme-linked immunosorbent assay (ELISA) will be used to measure serum levels of interleukin-1β (IL-1β), interleukin-6 (IL-6), interleukin-8 (IL-8), interleukin-10 (IL-10), interleukin-2 receptor (IL-2R), tumor necrosis factor-*α* (TNF-α), erythrocyte sedimentation rate (ESR), C-reactive protein (CRP), and plasma biomarkers including glial fibrillary acidic protein (GFAP), phosphorylated tau at positions 181, 217, and 231 (pTau181, pTau217, and pTau231), Aβ42 and Aβ40 and their ratios, and neurofilament light chain (NfL). These measurements will be conducted at baseline, 3 months, 6 months and 12 months.

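### The between-group tests named for continuous variables are unadjusted and the added GEE has no stated baseline term, so a 40-patient trial gives up precision its baseline measurements could supply

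*Protocol article*

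**What the plan says.** **Tests.** The Statistical analysis section states: "Continuous variables following a normal distribution will be compared using the independent samples" t-test, ANOVA or rank-sum test, "with a significance level of *p* < 0.05". It does not say whether raw follow-up values or changes from baseline are compared, and it names no covariate.

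**Longitudinal model.** The next paragraph of that section adds: "Generalized Estimating Equations (GEE) will be used to model outcome trajectories under the assumption of missing at random (MAR"). The model terms, the role of baseline and the model's rank against the simple tests are not stated. A baseline biomarker ratio is named there only as a predictor for imputing missing cognitive scores.

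**Baseline data.** For MMSE, MoCA, CDR, ADL, HAMA and HAMD-17, the Neuropsychological assessments section says: "These assessments will be conducted at baseline, 3 months, 6 months, and 12 months". For the cytokines and plasma markers, the Blood sample collection and analysis section says: "These measurements will be conducted at baseline, 3 months, 6 months and 12 months".

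**Size.** Under Sample size estimation, "this project targets 20 patients in each group". The number rests on precedent, because "Since no prior clinical studies have examined RIC in AD patients, there is no reference data available".

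**The concern.** A t-test, one-way ANOVA or rank-sum test compares arms without using each patient's own starting value as a covariate. For cognitive scales and blood markers that value usually predicts the follow-up value, and here it is collected for every patient. Leaving it out keeps between-patient variation in the error term that could have been removed.

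With 20 per arm, wide intervals are the main weakness of any comparison. The outcomes affected matter to the trial. HAMA and HAMD-17 serve the primary safety outcome. MMSE, MoCA, CDR and ADL are called primary efficacy endpoints in the abstract, although the Outcomes for efficacy section calls them secondary. The trial is meant to inform a Phase II study, so the precision of its estimates is part of what it delivers.

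The quoted sentence is also wrong on its face: it lists the rank-sum test among the methods for normally distributed variables.

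**Working it through.** **Inputs from the article.** N = 40, 20 per arm (Study design; Sample size estimation). Significance level 0.05 (Statistical analysis). Baseline and three follow-up visits for all scales and blood markers.

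**Assumptions.** Two-sided testing and 80% power for detectable differences. Equal SD at baseline and follow-up. All 40 patients analysed. The documents give no correlation ρ between baseline and follow-up, so a range of 0.3 to 0.8 is used.

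**The plan's own figure.** No effect size, SD or power lies behind N = 40, so there is no calculation to reproduce. For orientation, an unadjusted t-test on raw follow-up values with 20 per arm detects 0.91 SD with 80% power (noncentral t).

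**Formulas.** The variance of the treatment difference at one visit, relative to a t-test on raw follow-up values:
- change-score t-test: 2(1 − ρ)
- ANCOVA, including the small-sample cost of estimating the slope: (1 − ρ²) × (1 + 1/(N − 4)) = (1 − ρ²) × 37/36

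**Numbers put in.**
- ρ = 0.3: ANCOVA 0.91 × 37/36 = 0.935; change 1.4; ratio 0.935/1.4 = 0.668
- ρ = 0.5: ANCOVA 0.75 × 37/36 = 0.771; change 1.0; ratio 0.771
- ρ = 0.7: ANCOVA 0.51 × 37/36 = 0.524; change 0.6; ratio 0.874
- ρ = 0.8: ANCOVA 0.36 × 37/36 = 0.370; change 0.4; ratio 0.925

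| Assumed ρ | Variance cut by ANCOVA vs raw t-test | Variance cut by ANCOVA vs change-score t-test | Detectable difference: raw / change / ANCOVA (SD) | Raw-value t-test total N giving ANCOVA's variance |
|---|---|---|---|---|
| 0.3 | 6% | 33% | 0.91 / 1.08 / 0.88 | 43 |
| 0.5 | 23% | 23% | 0.91 / 0.91 / 0.80 | 52 |
| 0.7 | 48% | 13% | 0.91 / 0.70 / 0.66 | 76 |
| 0.8 | 63% | 7.5% | 0.91 / 0.58 / 0.55 | 108 |

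The last column is 40 divided by the ANCOVA variance ratio, for example 40/0.524 = 76.

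**Power at a true difference of 0.5 SD.** The raw t-test has 34% at every ρ. ANCOVA has 36%, 42%, 57% and 72% at the four values of ρ.

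**Where the advantage ends.** ANCOVA has lower variance than the raw t-test when (1 − ρ²) × 37/36 < 1, that is ρ² > 1/37, or ρ above about 0.16. It has lower variance than the change-score t-test when (1 + ρ)/2 × 37/36 < 1, that is ρ < 35/37, or about 0.95. Between those limits it has lower variance than both.

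**The case against.** **The GEE may already do this.** If baseline enters the GEE as a covariate, or as a response constrained to be equal across arms, most of the gain is recovered. If baseline is an unconstrained response, the contrast behaves like a change score. This is the strongest counterpoint, and it rules out saying that the plan certainly discards baseline. It does not clear the plan, because nothing in the article says that the GEE adjusts for baseline or takes precedence over the simple tests.

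**Covariates belong in the SAP.** The article is condensed and the SAP is not shown, so missing GEE terms alone would be no finding. But the article does fix the simple tests by name, and as named they are unadjusted.

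**The tests might be run on change scores.** The abstract speaks of improvements and of biomarkers before and after treatment, which fits that reading. A reader might infer a loss of a third to two thirds of the information by assuming raw follow-up values and high correlations. The text supports neither assumption. The loss against raw values is only about 6% at ρ = 0.3, and against change scores it shrinks as ρ rises. ANCOVA still gains on both readings across the assumed range.

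**Chance imbalance.** With simple randomisation the baseline difference has SD √(2/20) = 0.316, in SD units, so a gap above 0.3 SD arises about 34% of the time. A reader might infer bias or a raised false-positive rate. That does not follow: the unadjusted comparison is unbiased under randomisation, and its standard error already reflects chance imbalance. The cost is the precision loss already counted.

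**Reach and stakes.** It would be too wide to say that every outcome has a baseline: intolerance of the procedure and physical injury do not. The trial is presented as Phase I, for safety and feasibility, and has no power target. This lowers the urgency but does not argue against a better estimate from the same data.

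**Conclusion.** The concern holds as a loss of precision in the between-group comparison of continuous scales and blood markers. The named tests use no baseline covariate, the GEE has no stated one, and the main comparison is not identified.

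The size cannot be fixed from the documents. For assumed correlations of 0.3 to 0.8 and 20 per arm, the variance that adjustment would remove runs from about 6% to 63% if raw follow-up values are tested, and from about 33% down to 7.5% if change scores are tested. These ranges assume equal SDs at the two visits, no missing data, and a main analysis that does not already adjust for baseline. The point is a worthwhile improvement to the analysis and does not make the planned comparison invalid. The rank-sum wording is a separate, minor error.

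**What to change.** In the Statistical analysis section:

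1. Name one baseline-adjusted model as the main between-group comparison for each continuous scale and blood marker. Use either ANCOVA at each visit with the outcome's own baseline as covariate, or the planned GEE with that baseline as covariate and arm, visit and arm-by-visit terms. Analyse skewed biomarkers on the log scale.
2. Report the adjusted difference with its 95% confidence interval, and keep unadjusted means by arm and visit as description.
3. Reword the test sentence so that the rank-sum test applies to variables that are not normally distributed.

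The cost is a few sentences. All baselines are already scheduled, so no extra visits, samples or patients are needed. If the GEE is chosen, its robust standard errors should carry a small-sample correction, since there are only 40 patients.

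### The test rule ties the t-test, ANOVA and rank-sum test alike to normal data, leaves other variables without a rule, and as named makes no use of the baseline value of the blood markers

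*Protocol article*

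**What the plan says.** All of the following is in the protocol article.

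- **Test rule (Statistical analysis).** The sentence begins "Continuous variables following a normal distribution will be compared using the independent samples" and, after naming the t-test, ends "ANOVA, or rank-sum test, while categorical variables will be compared using the chi-square test". No separate clause covers continuous variables that are not normal.
- **Summaries (same section).** "Continuous and categorical data will be reported as mean values, standard deviations, number values, and percentages". No median, quartiles or geometric mean is mentioned.
- **Longitudinal model (same section).** "Generalized Estimating Equations (GEE) will be used to model outcome trajectories under the assumption of missing at random (MAR"). The scale, link and covariates are not given.
- **Endpoints (Outcomes for efficacy).** There are three classes of secondary outcome. One is plasma biomarkers (Aβ40, Aβ42, their ratio, pTau217, pTau181, GFAP, NfL) and one is serum inflammatory markers (six cytokine or receptor measures, ESR, CRP): 7 + 8 = 15 laboratory measures.
- **Timing (Blood sample collection and analysis).** Every marker is measured at baseline and at 3, 6 and 12 months.
- **Size (Sample size estimation).** "this project targets 20 patients in each group", on the precedent of earlier safety and feasibility studies: "Since no prior clinical studies have examined RIC in AD patients, there is no reference data available". No power, SD or effect size is stated for any marker.

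**The concern.** As written, the rule is wrong in one place and empty in another. It attaches a rank test to normal data, where it is not needed, and it says nothing about data that are not normal. Three tests are joined by an or, with no criterion for choosing between them, so with 15 markers and 20 values per arm the choice could be made after the data are seen. A mean and SD also describe a skewed concentration poorly at this size, since one or two high values can move both.

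The named two-group comparisons, taken as written, also leave out each patient's own baseline, although the trial pays to measure it.

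At stake are the precision and readability of the biomarker results, and the effect and SD estimates that a pilot passes on to the Phase II study the article foresees. The safety conclusion is not at stake.

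**Working it through.** **1. Figure to reproduce.** There is none: the article states no power for any endpoint. For orientation, at 20 per arm and two-sided 5% (sidedness assumed; the article gives "with a significance level of *p* < 0.05"), the standardised difference detectable with 80% power is (1.960 + 0.842) × √(2/20) = 0.886.

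**2. Assumptions.** The documents give no skew, effect size or correlation. Assumed here: log-normal marker, RIC halves the median (log shift ln 2 = 0.693), log-SD σ of 0.8 or 1.0, correlation ρ of 0.5 or 0.7 between log baseline and log follow-up.

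**3. Approximate formula.** On the log scale, power ≈ Φ(0.693 / (σ√(1−ρ²)) / √(2/20) − 1.96), with ρ = 0 for no baseline adjustment.
- σ = 1.0, unadjusted: 0.693/0.316 = 2.19; 2.19 − 1.96 = 0.23; 59%.
- σ = 1.0, ρ = 0.5: 0.693/0.866 = 0.800; 0.800/0.316 = 2.53; minus 1.96 = 0.57; 72%.
- σ = 1.0, ρ = 0.7: 0.693/0.714 = 0.971; 0.971/0.316 = 3.07; minus 1.96 = 1.11; 87%.

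The formula ignores the t distribution and the estimated slope, so simulation gives slightly less.

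**4. Simulated power** (20 per arm, two-sided 5%, marker halved):

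| Analysis | σ = 0.8 | σ = 1.0 |
|---|---|---|
| Raw t-test | 63–64% | 40–41% |
| Rank-sum test | 74–75% | 54–55% |
| Log t-test, no baseline | 76% | 57–58% |
| Log model with log baseline, ρ = 0.5 | 86% | 68–69% |
| Log model with log baseline, ρ = 0.7 | 96% | 83–84% |

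The ranges show the spread between repeated runs. Moving from rank-sum to log scale alone gains 2 to 3 points; adding the baseline gives most of the rest. Scale still matters within the adjusted model: raw-scale baseline adjustment at σ = 1.0 gives about 46% (ρ = 0.5) and 59% (ρ = 0.7), against about 69% and 84% on logs.

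**5. Where the effect of scale shrinks.** With the marker halved and σ = 0.5, the raw and log t-tests give 98% and 99%. With the shift set so that the log t-test has about 80% power, raw t / log t / rank-sum are 79/80/78% at σ = 0.2 and 78/80/78% at σ = 0.3. For a 30% reduction they are 55/60/58%, 29/35/33% and 14/19/18% at σ = 0.5, 0.7 and 1.0. The log scale therefore does not rescue a highly variable marker at this sample size.

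**6. Costs of logging.** If a marker is truly normal with CV 0.3, power falls from 80% to 73%; at CV 0.1 to 0.2 the loss is about 0 to 1 point. With σ = 1.0, a shift of 0.909 SD and 10% of control values below the detection limit, log t-test power is 78% if those values are set to half the limit and 68% if set to one hundredth of it.

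**The case against.** **The rank-sum test is named.** The sentence is probably a compressed form of the usual rule: t-test or ANOVA if normal, rank-sum otherwise. A reader might infer that the plan forces raw t-tests onto skewed data and so forfeits power that logs would regain. The document does not say that, and against the rank-sum test the log scale alone gains only 2 to 3 points. This objection stands. The literal wording still needs correcting, and a rank test reported beside a mean and SD is still a mismatch.

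**The GEE.** A reader might infer that it will run on raw concentrations. The article gives no scale, so this cannot be asserted; nor can it be excluded that baseline enters as one of the modelled visits.

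**Baseline through change scores.** The rank-sum test can be applied to changes. On the log scale, the change has variance 2σ²(1−ρ): at ρ = 0.5 this equals σ², no better than follow-up alone, and at ρ = 0.7 it is 0.60σ², against 0.51σ² with a covariate. So the objection stands in part.

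**Skew.** Its size is an assumption. Excluding patients with inflammatory conditions or with drugs that affect cytokines (Patient population) may trim extreme values. The raw t-test does not inflate false positives either: its simulated type I error was 0.029 to 0.051.

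**Scope.** The mean-and-SD sentence follows one on demographics and clinical characteristics and may concern only those tables. Transformation details often sit in an analysis plan, so their absence alone is no fault. What counts against the article is the rule it does state.

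**Conclusion.** The point holds as a badly fixed rule, with modest priority. The text conditions every continuous-data test on normality, gives other variables no test, names only mean and SD, and names comparisons that do not use the available baseline.

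Under the assumed values (halving, log-SD 0.8 to 1.0, correlation 0.5 to 0.7, 20 per arm), a baseline-adjusted log model has about 69% to 96% power, against 55% to 74% for the rank-sum test and 41% to 64% for a raw t-test. Most of the gain over the rank-sum test comes from the baseline covariate. At mild skew the choice of scale hardly matters.

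Two stronger conclusions are tempting and unsupported. One is that logging recovers lost power at no cost: it changes the estimand to a ratio, needs a detection-limit rule and loses some power if a marker is in fact normal. The other is that a trial conclusion is undermined: these endpoints are secondary in a safety and feasibility trial that claims no power for them.

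**What to change.** Reword the Statistical analysis section along these lines:

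- *Approximately normal continuous variables are compared by t-test or ANOVA and summarised as mean and SD. Other continuous variables, and ordinal or bounded scales, are compared by rank-sum test and summarised as median and quartiles.*
- *A table fixed before unblinding states, marker by marker, which concentrations (CRP, cytokines, GFAP, NfL, pTau and Aβ) are log-transformed. The same scale is used in every model, including the GEE, with log baseline as covariate. Results are RIC/sham geometric mean ratios with 95% CI.*
- *Values below the detection limit are handled by one stated rule for each assay.*

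The Aβ42/Aβ40 ratio and ESR need not be logged. The rank-sum test should stay as the main test for variables that are neither normal nor logged, so that ordinal and bounded scales such as CDR, ADL, HAMA and HAMD-17 keep a rule.

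Cost: wording only, with no new data, visits or assays. Tables for logged markers show ratios instead of differences, each assay needs a detection-limit rule, and some power is lost for any marker that turns out to be normal.
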